## Abstract

Introduction: Persistent Spinal Pain Syndrome Type 2 (PSPS-T2) is associated with changes in the brain’s pain processing. This is often due to problems with the body’s natural way of handling the pain management system. Exercise therapy, such as motor control and spinal stabilization, can help reduce pain and disability. However, exercise alone may not be sufficient. Approaches that consider both body mechanics and brain function are gaining popularity. Since brain changes play a role in muscle and bone problems, noninvasive brain stimulation (NIBS) is considered a helpful adjunctive treatment. Studies have shown that NIBS may help people with spinal pain and mood disorders. The aim of this study is to assess the impact of combining tDCS targeting the dorsolateral prefrontal cortex with spinal motor control exercises in patients diagnosed with PSPS-T2. This investigation is based on the hypothesis that such a combined intervention could result in a more significant reduction in disability. Methods/Materials: This randomized controlled trial (RCT) is structured as a double-blind, comparative, longitudinal design in accordance with the CONSORT guidelines. This RCT has been registered at ClinicalTrials.gov (NCT06969456). Forty-two participants diagnosed with PSPS-T2 will be randomized in a 1:1 ratio into two groups: tDCS + rehabilitation (E_tDCS_) or sham tDCS + rehabilitation (E_SHAM_). The intervention will use tDCS to deliver low-intensity direct current to modulate cortical excitability. The intervention will consist of 24 supervised sessions (2 per week, 60 min each) over 12 weeks. Neuromodulation and exercise protocols will be adapted to the intervention phases based on previous research. The sample size has been calculated using GPower^®^, assuming an effect size of 0.81, α = 0.05, power = 0.95, and a 40% dropout rate. Data will be collected from October 2025 to January 2027. Impact Statement: This study integrates neurophysiological modulation via tDCS with targeted exercise therapy, presenting an innovative approach to enhance pain modulation, functional recovery, and cortical reorganization in patients with PSPT-2. This approach has the potential to inform future evidence-based strategies for neurorehabilitation and pain management.

## 1. Introduction

Chronic spinal pain is one of the leading causes of disability worldwide, affecting between 15% and 30% of the adult population. It represents a major burden on healthcare systems and the economy, with high direct and indirect costs associated with medical treatments, productivity loss, and work absenteeism [1]. In recent years, there has been a paradigm shift in the understanding of chronic pain, moving from purely structural diagnoses to a more biopsychosocial model of care. This transition is reflected in the adoption of the term “chronic primary pain” in the ICD-11 classification by the World Health Organization [2]. The goal of this shift is to avoid overmedicalization, reduce stigma, and foster a more person-centered and integrative approach to pain management. Additionally, it aims to improve interdisciplinary communication and facilitate access to more appropriate treatments [2]. This conceptual shift has also impacted the definition and classification of chronic spinal pain syndromes, resulting in the adoption of novel terminologies and diagnostic frameworks.

Traditionally, the term “Failed Back Surgery Syndrome” (FBSS) has been used to describe individuals who continue to experience chronic pain after one or more spinal surgeries. However, this terminology has been criticized for its negative and stigmatizing connotations, as it implicitly suggests failure on the part of the surgery, surgeon, or patient [3]. In response, a more neutral term, Persistent Spinal Pain Syndrome (PSPS), has been proposed [4]. This evolution in terminology highlights the critical role of language in influencing clinical perceptions and shaping patient identity. This updated classification, endorsed by the International Association for the Study of Pain (IASP) and included in the ICD-11 [5], differentiates between PSPS Type 1 (persistent pain without prior surgery) and PSPS Type 2 (persistent pain following surgical intervention) [4,6]. The aim is to promote clearer clinical communication, reduce stigma, and support a more comprehensive biopsychosocial approach to care [6,7]. Among these subtypes, PSPS-T2 represents a particularly challenging condition, as it affects a significant segment of the population and is believed to arise from complex interactions involving neuroplastic changes in the central nervous system, as well as various biological, psychological, and social factors [8].

Notably, the prefrontal cortex (PFC), a brain region responsible for decision-making, emotion regulation, and executive control, shows structural and functional alterations in individuals with chronic pain [9,10,11]. Neuroimaging studies have consistently demonstrated reduced gray matter volume, particularly in the dorsolateral prefrontal cortex (DLPFC), along with disrupted functional connectivity with key pain-related regions, such as the amygdala, thalamus, and insula [12,13,14]. These alterations may contribute not only to increased pain perception but also to cognitive and affective dysfunctions. Patients with PSPS-T2 frequently exhibit impairments in working memory, executive function, and attentional control [15]. Neurochemical imbalances, including altered dopamine and glutamate levels, may further exacerbate pain and mood dysregulation [16]. Collectively, these findings underscore that chronic pain should not be perceived merely as a sensory phenomenon but rather as a condition encompassing significant neurocognitive and emotional dimensions.

These findings highlight the relevance of integrative treatment strategies targeting both the neurocognitive and sensory dimensions of chronic pain. Approaches such as cognitive–behavioral therapy (CBT), structured physical exercise, and pain neuroscience education have shown promise in promoting adaptive neuroplasticity and restoring functional brain connectivity [17,18]. In this context, understanding the brain’s involvement in pain modulation is crucial for developing multimodal interventions. In this context, the central nervous system is a key player in the development and maintenance of musculoskeletal function.

This has led to growing interest in neuromodulation techniques, such as NIBS, for chronic pain management [19]. Among these, tDCS has emerged as a low-risk, noninvasive intervention that modulates cortical excitability by delivering weak electrical currents to the targeted brain regions. When combined with physical exercise or CBT, tDCS can reduce pain intensity and improve functional outcomes in patients with chronic lower back pain [20]. Although its efficacy as a standalone treatment remains limited, personalized stimulation protocols show promise in addressing both the nociceptive and emotional components of chronic pain [21]. Thus, the integration of cortical neuromodulation with exercise-based interventions may constitute a synergistic approach that optimizes neuroplastic adaptation and enhances pain relief. Therefore, the combination of cortical neuromodulation and spinal motor control exercise could enhance therapeutic outcomes and offer alternatives for patients who are not candidates for or have not responded to conventional treatments. Based on this rationale, the objective of this study is to evaluate the effect of combining tDCS targeting the DLPFC with spinal motor control exercise in patients diagnosed with PSPS-T2.

## 2. Materials and Methods

### 2.1. Study Design

This study has been designed as an RCT that adopts a double-blind, comparative, longitudinal, and prospective design. This study will adhere to the SPIRIT statement guidelines (Table 1) [22]. The findings will be reported according to the TIDieR Checklist [23]. This study will be a research protocol for two groups: the E_tDCS_ (experimental group) and E_SHAM_ (control group). Data will be collected from October 2025 to January 2027. All participants will sign an informed consent form prepared in accordance with the ethical guidelines of the Declaration of Helsinki [24]. The study protocol was approved by the Ethics Committee of the Catholic University of Valencia on 28 January 2025 (ID: UCV/2024-2025/031). Once approval was obtained from the corresponding institutional ethics committee, the study was registered in the official ClinicalTrials.gov database under the registration number (NCT06969456).

### 2.2. Study Population

The participants will be patients diagnosed with chronic spinal pain, specifically PSPS-T2, according to the diagnostic criteria recently established by Van de Mikelis et al. [25] and aligned with the International Association for the Study of Pain classification. The diagnosis of PSPS-T2 is based on the patient’s history, clinical examination, and medical imaging. Diagnoses will be made by orthopedic surgeons or rheumatologists specialized in spinal disorders, and only those who meet the specific indications for noninvasive neuromodulation and exercise interventions will be included. Patients will be recruited through direct referral by these medical specialists, as well as through public announcements advertising “a new study on chronic spinal pain.” Recruitment will be promoted using flyers and posters distributed throughout Valencia (Spain) and posts on popular social media platforms such as LinkedIn, Facebook, and Instagram. All potential participants will receive detailed information about the study procedures, and those expressing interest will receive a brief overview of the screening process. Participants will be selected based on the predefined eligibility criteria.

### 2.3. Inclusion and Exclusion Criteria

The inclusion criteria for participant eligibility have been defined to ensure a homogeneous sample of individuals experiencing chronic spinal pain, consistent with the PSPS-T2. Participants are required to meet the following conditions: (i) a confirmed diagnosis of PSPS-T2; (ii) the presence of neuropathic pain, as indicated by a score of ≥4 on the Neuropathic Pain Diagnostic Questionnaire (DN4); (iii) an age of over 18 years at the time of enrolment; (iv) a minimum duration of pain of six months, to ensure chronicity of symptoms; and (v) a self-reported pain intensity of ≥7 on the Visual Analogue Scale (VAS), reflecting a moderate to severe level of pain. Exclusion criteria have been established to minimize potential confounding factors and ensure the safety of the participants. Individuals are excluded if they meet any of the following conditions: (i) history of prior abdominal surgery or planned surgical procedure in the abdominal region during the study period; (ii) current pregnancy or breastfeeding, due to potential physiological and hormonal influences on pain perception and treatment response; (iii) presence of severe fractures or other significant medical pathologies that could interfere with participation or confound outcome measures; (iv) structural deformities of the spine, such as scoliosis or congenital anomalies, which could alter the biomechanical context of pain; and (v) diagnosed neurological or psychiatric disorders that might affect cognitive function, adherence to intervention protocols, or accurate self-reporting of pain.

### 2.4. Procedure

Upon formation of the groups, four distinct sample collections will be undertaken at the following intervals: Pre, Post-1 month, Post-3 months, and Post-6 months (Figure 1). At each designated measurement point, a comprehensive follow-up of the studied variables will be meticulously conducted and recorded in the “Data Collection Notebook”. This document is specifically crafted to capture both primary and secondary variables, thereby ensuring a systematic approach to data collection throughout the study. The research comprises two groups, each structured to meet the previously outlined objectives: the E_tDCS_ and E_SHAM_ groups. All assessments will be performed bilaterally to enable within-subject comparisons.

## 3. Randomization and Blinding

Participants will be randomly allocated to either the intervention or control group through a stratified randomization process to ensure a balanced distribution based on neuropathic pain levels. Baseline neuropathic pain will be evaluated using the Douleur Neuropathique 4 (DN4) questionnaire, resulting in the formation of two strata: Subgroup 1, with DN4 scores of 4–7, and Subgroup 2, with DN4 scores of 8–10. An independent researcher will generate the randomization sequence, which will be securely stored on an encrypted USB device with restricted access, to be accessed solely for participant allocation. The study will employ a double-blind design, with participants blinded via a sham intervention and outcome assessors blinded to group allocation, without involvement in the intervention delivery. Additionally, follow-up data will be collected and recorded by the same independent researcher to ensure impartiality and data integrity. All intervention sessions will be conducted by experienced physiotherapists, each with over ten years of expertise in neuromodulation and exercise therapy for chronic lower back pain, ensuring consistent application of the treatment protocols.

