### 5.2. Primary Outcome

#### Disability

The ODI is the most widely used and validated instrument for assessing functional impairment resulting from low back pain [35]. This self-administered questionnaire encompasses ten domains that evaluate limitations in activities of daily living [36]. Each domain is scored on a scale of 0–5, with higher scores indicating greater disability. The total ODI score is derived by summing the individual domain scores, dividing by the maximum possible score, and expressing the result as a percentage (e.g., a summed score of 25 out of 50 yields 50%) [37]. The Spanish version of the ODI has undergone psychometric validation, demonstrating high sensitivity and specificity in assessing the functional status of individuals with low back pain [38]. Psychometric evaluations revealed that the ODI exhibited strong construct validity and satisfactory internal consistency. Furthermore, the ODI has demonstrated high test–retest reliability, with correlation coefficients ranging from 0.73 to 0.99, depending on the interval between assessments [39].

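### As worded, the person who generates the randomisation sequence also collects the follow-up data, so the claimed blinding of outcome assessors is not secured

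*Protocol article*

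**What the plan says.** All the relevant statements stand in one paragraph, Section 3 of the protocol article (Randomization and Blinding).

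- Sequence: "An independent researcher will generate the randomization sequence, which will be securely stored on an encrypted USB device with restricted access", and the device is "to be accessed solely for participant allocation".
- Blinding: the trial is called double-blind, with "participants blinded via a sham intervention and outcome assessors blinded to group allocation, without involvement in the intervention delivery".
- Follow-up, in the next sentence: "Additionally, follow-up data will be collected and recorded by the same independent researcher to ensure impartiality and data integrity".

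Three other places bear on the consequences. Section 5.2 describes the primary outcome, the Oswestry Disability Index (ODI): "This self-administered questionnaire encompasses ten domains that evaluate limitations in activities of daily living". Section 8.1 has unfinished submissions removed. Section 8.2.2 makes the analysis per-protocol, with intention-to-treat only in the event of attrition or loss of power, and Section 4 allows for 40% dropout.

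**The concern.** A person who wrote the allocation list cannot be presumed blind to it. If that person also collects and records the follow-up outcomes, the assessor half of the double-blind claim depends on safeguards that the article does not describe.

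The claim carries weight here. Double-blinding is stated in the Abstract, in Section 2.1 and in Section 3, and readers will judge the risk of detection bias from it. Blinding also cannot be restored for data that an unblinded person has already collected, so the point has to be settled before the follow-up visits take place.

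**Working it through.** The plan gives no figure on this point, so the check is a reading of the text.

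**1. Who is the same independent researcher?** Section 3 introduces people in this order:

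| Order | Role | Task |
|---|---|---|
| 1 | An independent researcher (singular) | Generates the sequence |
| 2 | Outcome assessors (plural) | Blinded, not delivering treatment |
| 3 | The same independent researcher (singular) | Collects and records follow-up data |
| 4 | Physiotherapists | Deliver the sessions |

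The third entry needs an antecedent. The first entry is the only one with the same noun, adjective and number. The assessors are plural and are never called independent researchers. The independent statistician of Section 8.2.2 appears much later and is described as uninvolved in data collection, so that role cannot be meant.

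**2. Does the storage safeguard separate the roles?** It protects the stored file and limits its use to allocation. It does not say who holds the device, who makes the allocations, or that the generator is denied access once the list exists. It neither shows that the collector knows each arm nor rules it out.

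**3. Does any other section separate them?** Section 2.4 (Procedure) describes the data notebook but not who fills it in. Section 8.1 gives oversight of data management to the study coordinator. Section 8.2.2 separates only the statistician from data collection. None of these separates sequence generation from follow-up.

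**4. How could knowledge of the arm reach the data?**

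- *Primary outcome.* The ODI is completed by the participant, who is blinded by sham. The collector does not make the rating.
- *DN4.* Section 5.3.7 has participants asked to describe their pain against the first seven descriptors. That is elicited in person and is the most direct route, though for a secondary outcome.
- *Completeness.* Unfinished submissions are removed (Section 8.1). Whoever collects the forms influences which are finished and so kept.
- *Retention.* With 40% dropout allowed for and a per-protocol analysis, differential effort in chasing missed visits or incomplete forms could change who is analysed in each arm. This could affect even a fully self-reported ODI.

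**5. Can the size be derived?** No. The document gives nothing from which to estimate a shift. Purely to show scale, assume that unblinded collection moves one arm by b standard deviations when the true effect is zero. Take a two-sided 5% two-sample t-test with n per arm, df = 2n − 2 and noncentrality b × √(n/2). For n = 21 (all 42 participants) and b = 0.2, the noncentrality is 0.2 × √10.5 = 0.65.

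| Assumed shift b | Type I error, 21 per arm | Type I error, 15 per arm |
|---|---|---|
| 0.1 SD | 6.2% | 5.8% |
| 0.2 SD | 9.7% | 8.3% |
| 0.3 SD | 15.8% | 12.5% |

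The 15-per-arm column uses the total of 30 calculated in Section 4 before the dropout allowance. The shifts are assumptions, and the simple t-test stands in for the planned repeated measures ANOVA.

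**The case against.** The strongest reply is that the sentence is loosely worded and no design fault lies behind it. It directly follows the statement on blinded assessors, opens as an addition to it, and gives impartiality as its purpose. The authors may have meant that one consistent, blinded assessor records every follow-up visit. That is possible, and intent cannot be settled from the text. It does not rescue the wording, because no such assessor has been introduced for the same to refer to. The sentence needs correcting under either reading.

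Three further objections stand and limit the point.

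- A reader might infer that this person holds the list and knows every participant's arm at follow-up. The article does not say so. The list is on a restricted-access device, and generating a sequence is not the same as knowing each enrolled participant's arm months later.
- A reader might infer that the ODI comparison is directly compromised. It is self-administered by sham-blinded participants, so any bias is indirect.
- A reader might infer that the collector will reveal the arm to participants and so break the sham. Nothing in the document suggests disclosure. The treating physiotherapists, who see participants over 24 sessions, are not listed as blinded either, so the collector adds little to that route.

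The type I error figures cannot support a severity rating, since they rest on chosen shifts.

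**Conclusion.** The point holds as an internal contradiction in Section 3. On its plain wording one person generates the sequence and collects the follow-up data, while the same paragraph claims blinded outcome assessors, and no other section separates the two tasks. The claim of assessor blinding is therefore not secured. The document does not go further and show that outcome assessment is in fact unblinded or that participant blinding fails.

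The conclusion rests on the ordinary antecedent of the sentence and on the absence of any statement that the generator lacks access to or knowledge of the sequence. It covers all scheduled follow-up visits. The resulting bias is of unknown size and would act mainly through the DN4 interview items, the handling of forms and differential completeness. It should be resolved because the remedy is cheap and the loss of blinding would be irreversible.

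**What to change.** Rewrite Section 3 so that the tasks belong to different people.

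1. The sequence generator only prepares the list and releases assignments to the treating physiotherapists, and has no contact with participants or outcome data.
2. The blinded outcome assessors already named in that section collect and record all baseline and follow-up data, and have no access to the sequence.
3. State who holds the encrypted device, and that no one who collects outcomes can open it.

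If the intended meaning was one consistent blinded assessor across visits, say so and state that this person is not the sequence generator.

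The cost is a change of wording and, if one person was in fact to do both, a reassignment of tasks among existing roles. Sample size, visit schedule and analysis do not change.

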## 4. Sample Size

The sample size will be determined using G*Power software (Franz Faul, University of Kiel, Kiel, Germany; version 3.1.9.2). Statistical analysis will be conducted using repeated measures analysis of variance (ANOVA). The calculation will be based on the primary outcome variable, the Oswestry Disability Index (ODI), with the assumption of a Cohen’s effect size of 0.81 [26], a statistical power of 0.95, an alpha error of 0.05, and two study groups. The estimated total sample size is 30. To accommodate a potential dropout rate of 40% during follow-up, the minimum required number of participants has been adjusted to 42 (experimental group = 21; control group = 21). This rate is consistent with previous evidence: a review of clinical studies on chronic pain reported that dropout can vary widely, ranging from 5% to 60% depending on the study, type of pain, duration, and intervention. The selected effect size is categorized within a large range (0.60–1.19), as corroborated by previous studies [27].

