From a methodological standpoint, there is a clear need for more rigorous experimental designs incorporating placebo-controlled and double-blind procedures, as well as longitudinal assessments, to determine the durability of tDCS effects. Moreover, the integration of complementary approaches, such as functional neuroimaging and computational modelling of electric fields, may provide deeper insights into the neurophysiological mechanisms underlying stimulation and its network-dependent effects [73]. Advances in individualized stimulation protocols, task-specific coupling, and parameter optimization are expected to enhance the therapeutic and cognitive efficacy of tDCS, potentially leading to more robust and reproducible clinical outcomes.

A minor limitation of this study is the potential effect of participant dropout on statistical power. Although the sample size has been calculated with conservative assumptions and includes an adjustment for expected attrition, and measures have been implemented to enhance adherence, some reduction in effective power cannot be entirely excluded. This should be considered when interpreting these findings. Integrating these insights, future studies should consider the combined application of tDCS with task-specific exercises or cognitive interventions to maximize neuroplastic effects. This approach may help overcome some of the current limitations of tDCS, such as variability in individual responses, and provide more targeted and sustained benefits in both clinical and experimental contexts. Additionally, reporting standardized protocols and multimodal outcome measures—behavioral, neurophysiological, and imaging-based—will be essential to build a more consistent and generalizable evidence base for the clinical application of tDCS.

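### The 40% dropout allowance is applied as 30 × 1.4 = 42 instead of 30 / 0.6 = 50, so if 40% do drop out, about 25 completers remain, not the 30 behind the stated 0.95 power

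*Protocol article*

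**What the plan says.** Section 4 (Sample Size) bases the calculation on the primary outcome, the Oswestry Disability Index. The named method is repeated measures ANOVA, "with the assumption of a Cohen’s effect size of 0.81", "a statistical power of 0.95, an alpha error of 0.05, and two study groups". The result before any allowance for loss is: "The estimated total sample size is 30". The allowance follows: "To accommodate a potential dropout rate of 40% during follow-up, the minimum required number of participants has been adjusted to 42", split as "experimental group = 21; control group = 21".

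The Abstract gives 42 participants randomised 1:1 and describes the calculation as "assuming an effect size of 0.81, α = 0.05, power = 0.95, and a 40% dropout rate". Section 10 (Discussion) says: "Although the sample size has been calculated with conservative assumptions and includes an adjustment for expected attrition", while conceding that some loss of power is still possible.

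**The concern.** The three printed numbers (30 needed, 40% lost, 42 randomised) do not fit together. Section 4 and the Abstract lead a reader to believe that the trial keeps 0.95 power after 40% dropout. That requires 30 patients to remain out of 42, and losing 40% of 42 leaves fewer than 30. What is at stake is the accuracy of a stated design property. The published power is attached to a number of completers that the design does not deliver under its own dropout assumption. The Discussion then tells readers that attrition has been allowed for.

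**Working it through.** **Inputs** (Section 4, with the effect size, alpha, power, dropout rate and total of 42 repeated in the Abstract): total needed 30; dropout 40%; randomised 42 (21 + 21); power 0.95; alpha 0.05; effect size 0.81.

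**1. Reproduce the plan's figure.** n × (1 + d) = 30 × 1.40 = 42. This matches exactly, so the allowance was added as a percentage of the completers.

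**2. The inflation that preserves 30.** Completers = randomised × (1 − d), so randomised = n / (1 − d) = 30 / 0.60 = 50, or 25 per arm. The stated total is 8 lower.

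**3. What 42 delivers.**
- Expected completers at 40% dropout: 42 × 0.60 = 25.2, about 12 to 13 per arm. The shortfall is 30 − 25.2 = 4.8, or 16% of 30.
- Largest dropout that still leaves 30: 1 − 30/42 = 28.6%.
- If each participant independently has a 40% chance of dropping out (an assumption), the probability of keeping at least 30 of 42 is about 0.09 (binomial).

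**4. Effect on power.** Section 4 does not say which effect is tested, how many measurements and what between-visit correlation were entered, or whether 0.81 is d or f. The visit count is not settled elsewhere either: Section 2.4 lists four assessments and Section 8.2.2 lists five. The power at 25 therefore cannot be derived from the article.

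To gauge the size of the loss, I took two settings that each return exactly 30 at 0.95 power. Both are assumptions. Both read 0.81 as d, so f = 0.81 / 2 = 0.405, and test group × time with a noncentral F on (m − 1) and (N − 2)(m − 1) degrees of freedom, where N is the total and m the number of measurements.

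| Assumed setting | Noncentrality | Power at 30 | Power at 25 |
|---|---|---|---|
| m = 2, correlation ρ = 0.3 | f² N m / (1 − ρ) | 0.951 | 0.906 |
| m = 5 | f² N (m − 1) | 0.953 | 0.904 |

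The two routes agree on a fall from 0.95 to about 0.90. Steps 1 to 3 do not depend on either setting.

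**The case against.** **The 40% is only a possibility.** Section 4 calls the rate potential and cites a range of 5% to 60%; at losses up to 28.6%, 42 is enough. This stands, and it is why the shortfall is stated conditionally. But 40% is the rate that the plan says it accommodates, and 42 does not accommodate it.

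**The loss is modest.** Under both settings that return 30, power at 25 stays near 0.90, above the 80% threshold in Section 8.2.2. The Discussion also warns that some loss of power cannot be excluded. This stands too and limits the consequence. It does not make the stated combination of 42, 40% and 0.95 correct.

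**Dropouts may still be analysed.** Section 8.2.2 plans a per-protocol analysis and turns to intention-to-treat if there is attrition or power falls below 80%. The analysed set may therefore not be completers alone. The article names no method for missing outcomes, however, and the fallback cannot supply data that were not collected. Complete follow-up would still come from about 25 people.

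**Stronger readings.** A reader might infer that power collapses well below 0.80, that 0.95 at 30 holds only with a high between-visit correlation, or that a null result is bound to be over-interpreted. The documents support none of these. Low power values come from assuming a particular pattern of effect over time, or a single-visit two-arm comparison, neither of which Section 4 states; they mostly reflect doubt about the 30 itself, not the dropout step. No particular correlation is required, since more than one setting returns 30. A fall to about 0.90, with a caveat printed in the Discussion, does not establish over-interpretation.

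**Conclusion.** The dropout adjustment is wrong as written. It uses multiplication where division is needed, and no other section redefines the 40% or sets a different target for completers. The total is 8 short of the 50 that the stated assumptions require, and about 5 completers are missing if 40% dropout occurs. This part rests only on printed figures and on the ordinary meaning of a dropout rate.

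The cost in power is not determined by the article. The estimate of 0.95 falling to about 0.90 rests on the two assumed settings above, and only the sponsor's original G*Power inputs can settle it. The error misstates a design property but does not by itself undermine the trial.

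**What to change.** 1. **Section 4 and Abstract.** State that 42 randomised preserves 30 completers, and hence the 0.95 power, only up to about 28.6% dropout. State that about 25 completers are expected at 40%, and give the power for 25 recomputed from the original G*Power inputs.
2. **Discussion.** Remove the wording that the calculation is conservative and adjusts for expected attrition, or qualify it to match the restated figures.
3. **Alternative.** If the 40% and 0.95 claims are both kept, the matching size is 50 (25 per arm).

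Restating is a text correction: it needs no extra patients, and the stated power becomes somewhat less favourable. The alternative costs 8 more participants.
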